#### Serum markers

[The evaluation schedule: at baseline, 6 months from the baseline (± 1 month), and 12 months (± 1 month)]. Insulin resistance will be assessed using the HOMA-IR index [fasting insulin (µIU/mL) × fasting glucose (mmol/L)/405]. The serum tumor markers CEA and CA 15 − 3 will be measured using chemiluminescent enzyme immunoassays (Roche, IN, USA). TNF-α levels will be measured using a commercially available enzyme-linked immunosorbent assay (R&D, Minneapolis, MN, USA). High-sensitivity C-reactive protein (hs-CRP) levels will be measured using a latex-enhanced immunoturbidimetric assay using an ADVIA 1650 chemistry system (Bater). Adiponectin level will be measured using an enzyme immunoassay kit (Mesdia, Seoul, Korea). Serum levels of fasting glucose, total cholesterol (TC), triglycerides (TG), and high-density lipoprotein cholesterol (HDL-C) will be measured from serum using an ADVIA 1650 chemistry system (Siemens, NY, USA).

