**Methods:**

This 12-month RCT includes 96 patients with (stages 1–3) breast cancer randomly assigned to the exercise or control groups. Participants in the exercise group will receive an exercise program tailored to their phase of treatment, type of surgery, and physical function. During post-operative recovery, exercise interventions will be emphasized to improve shoulder range of motion (ROM) and strength. During chemoradiation therapy, exercise intervention will focus on improving physical function and preventing loss of muscle mass. Once chemoradiation therapy is completed, exercise intervention will focus on improving cardiopulmonary fitness and insulin resistance. All interventions will be home-based exercise programs supplemented with once-monthly exercise education and counseling sessions. The main outcome of the study is fasting insulin level at baseline, 6 months, and 1 year post-intervention. Our secondary outcomes include shoulder ROM and strength at 1 month and 3 months, body composition, inflammatory markers, microbiome, QoL, and physical activity levels at 1 month, 6 months, and 1 year post-intervention.

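### The HOMA-IR formula pairs glucose in mmol/L with 405, the divisor for mg/dL, so unit and constant are inconsistent and values are 18 times too small if it is applied as written

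*Protocol article*

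**What the plan says.** The Serum markers section states: "Insulin resistance will be assessed using the HOMA-IR index". It gives the formula in square brackets as "fasting insulin (µIU/mL) × fasting glucose (mmol/L)/405". The part at issue is the pairing of unit and divisor, "fasting glucose (mmol/L)/405".

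The same section describes the glucose assay: "Serum levels of fasting glucose, total cholesterol (TC), triglycerides (TG), and high-density lipoprotein cholesterol (HDL-C) will be measured from serum", on a named analyser system. It gives no reporting unit for glucose and no conversion step, and the formula appears nowhere else in the article.

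HOMA-IR sits among the secondary and ancillary measures. The primary outcome is insulin itself. The abstract puts it as "The main outcome of the study is fasting insulin level at baseline, 6 months, and 1 year post-intervention", and Primary outcome measures marks the 12-month value as primary.

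**The concern.** HOMA-IR is a named index with a fixed scale, and its divisor depends on the glucose unit. The divisor 405 belongs to mg/dL, but the formula states mmol/L. The two cannot both be right, and nothing else in the article shows which one is the slip.

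At stake is the absolute scale of the only index the article gives for insulin resistance. Insulin resistance is a stated target of the exercise after chemoradiation (abstract) and is named in the trial's aim in the Discussion. If the line is coded literally, the reported means, differences and confidence limits would be on a scale that is not HOMA-IR, and a reader could not set them beside those of other studies. A published formula is also easily copied into analysis code and into the results paper.

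**Working it through.** **Inputs**

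- From the article (Serum markers): insulin in µIU/mL, glucose in mmol/L, divisor 405.
- Not in the article: the molar mass of glucose, 180.156 g/mol, and the standard HOMA-IR divisor for mmol/L, 22.5. The second is the definition of the index, not a trial-specific figure.
- The insulin and glucose pairs below are assumed for illustration.

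**Step 1. Unit conversion.** 1 mmol/L of glucose = 180.156 mg/L = 18.016 mg/dL, conventionally 18.

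**Step 2. Reproduce the plan's divisor.** With glucose in mg/dL, the divisor is 22.5 × 18 = 405 (405.4 with the unrounded factor). So 405 is reproduced under mg/dL. Under the stated mmol/L the divisor is 22.5, and 405 is not reproduced.

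**Step 3. Size of the discrepancy.** As written over standard = (insulin × glucose / 405) ÷ (insulin × glucose / 22.5) = 22.5/405 = 1/18. Insulin and glucose cancel, so the factor is the same for every participant and visit.

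**Step 4. Examples (assumed values)**

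| Insulin (µIU/mL) | Glucose (mmol/L) | As written, /405 | Standard, /22.5 | Ratio |
|---|---|---|---|---|
| 5 | 4.5 | 0.056 | 1.00 | 18 |
| 10 | 5.0 | 0.123 | 2.22 | 18 |
| 15 | 5.5 | 0.204 | 3.67 | 18 |
| 25 | 7.0 | 0.432 | 7.78 | 18 |

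For the second row in mg/dL: 5.0 × 18 = 90, and 10 × 90/405 = 2.22, which agrees with the /22.5 result.

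**Step 5. Plausibility.** At glucose 5 mmol/L, the formula as written reaches 1 only at insulin 405/5 = 81 µIU/mL. The standard formula reaches 1 at 22.5/5 = 4.5 µIU/mL.

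**Step 6. Effect on tests.** Dividing all values by 18 divides each mean difference and its standard error by 18, so t is unchanged. The same holds for the F statistics of the repeated-measures ANOVA and of the ANCOVA, where outcome and baseline are rescaled together. A check on simulated data (40 per group) gave t = 3.095 and p = 0.0027 both before and after division by 18. Percentage changes are also unaffected, since the factor cancels.

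**The case against.** The strongest reply is that this may be no more than a wrong label. The constant printed is the mg/dL constant. If the laboratory reports mg/dL and the analyst enters that number, every value is correct. This stands: the article gives no reporting unit, so a reader who infers that the trial's HOMA-IR values will be 18 times too small goes further than the text allows. That holds only if glucose in mmol/L is entered.

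The second reply is that no group comparison would change. This also stands, by step 6. The harm is confined to absolute values and to comparison with other studies.

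The third is that little hangs on the index. Fasting insulin is the primary outcome, and the Sample size section rests on insulin levels. HOMA-IR is not named in the secondary objective or in the list of variables in Statistical analysis methods. That limits the weight of the point, although insulin resistance does feature in the stated aims.

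Two further consequences might be inferred, and the article supports neither:

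- **Participants would all fall below a HOMA-IR cut-off.** The article sets no HOMA-IR threshold for eligibility, outcome definition or analysis.
- **Mixed units between visits or laboratories would produce spurious 18-fold changes.** Recruitment is from one hospital and glucose is assigned to one analyser system; nothing points to mixed units.

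What none of these replies does is make the printed formula right.

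**Conclusion.** The formula is internally inconsistent as printed, and nothing in the article corrects it. The size depends on one fact that the article does not give:

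- Glucose entered in mmol/L: all absolute HOMA-IR values, mean differences and confidence limits are too small by a factor of 18.
- Glucose entered in mg/dL: the values are right and only the unit label is wrong.

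In neither case do p-values, percentage changes, the primary outcome or the sample size change. The finding rests on the standard definition of HOMA-IR and on the molar mass of glucose; it does not depend on the illustrative values.

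The grade is should-fix: an outcome formula that is wrong as written, for a secondary marker. It does not threaten the trial's primary conclusion, and it can be put right even after data collection as long as insulin and glucose are kept as separate values.

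**What to change.** Establish the unit in which the laboratory reports fasting glucose and state it in Serum markers. Then print the matching version of the formula:

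- insulin (µIU/mL) × glucose (mg/dL) / 405, or
- insulin (µIU/mL) × glucose (mmol/L) / 22.5.

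Check that the analysis code uses the same pairing, for instance by running it on one participant whose value has been worked out by hand.

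The cost is one line of text and, at most, one line of code. No new data, extra participants or change to the planned tests are needed.

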#### Nutritional status and Microbiome analysis

[The evaluation schedule: at baseline, 6 months from the baseline (± 1 month), and 12 months (± 1 month)]. Several studies have suggested that the gut microbiota is mainly driven by nutritional status [40–42]. Participants’ nutritional status will be measured using a food frequency questionnaire (FFQ). The FFQ was based on food records from the Korea Health and Nutrition Examination Survey (KHANE) in 1998 and consisted of 109-food based questions and 29-dish based questions [43]. The FFQ has a reasonable relative validity for nutrient intake in Korean adults [43]. Stool samples will be collected by patients and the samples will be stored at − 80 °C until analysis. The total DNA will be extracted directly from the fecal samples using the FastDNA SPIN Kit for Soil (MP Biomedicals, Santa Ana, CA, USA), following the manufacturer’s instructions. Polymerase chain reaction (PCR) will be used to amplify the V4 region of the 16 S rRNA gene, which will be analyzed using Illumina MiSeq DNA sequencing. The data will be analyzed using the EzBioCloud system (www.ezbiocloud.net). Microbiome analyses, including quality control, OUT picking, sequence databases, and sequencing primers, will be performed according to the protocol described by Yoon et al. [44].

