#### Secondary objective

To evaluate the effect of the exercise program on changes in shoulder function, body composition, QOL, patient-reported outcomes, and the diversity and composition of the gut microbiome after an exercise intervention.

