**ASSESSMENTS**					
Body composition	○		○	○	○
Shoulder ROM & Strength	○		○	○	○
Physical activity	○		○	○	○
SPADI	○		○	○	○
Serum markers	○			○	○
Microbiome analysis	○			○	○
Nutritional status	○			○	○
QOL	○		○	○	○

Notes. POD, post-operative day; ROM: Range of motion; SPADI: Shoulder pain and disability index; QOL: Quality of life

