#### Statistical analysis methods

All analyses will be performed using the SPSS version 26.0 software (IBM Corp., Armonk, NY, USA). A Chi-square test for categorical variables and an independent t-test for continuous variables will be used to test group differences at baseline. Two-way repeated-measures ANOVAs will be conducted to observe the effects of the intervention on fasting insulin levels, shoulder ROM and function, body composition, inflammatory markers, microbiome, QOL, and physical activity levels. Paired t-tests will be performed to examine the difference between outcome measurements and baseline values, while independent t-tests will be employed to examine group differences in variables at each time point. The Bonferroni correction method will be used to correct for multiple tests. Analysis of covariance (ANCOVA) will be applied to test the effect of an exercise intervention on body composition, PA, and complications, since these variables will be measured after adjusting for baseline values. First, from baseline to 1 month from the baseline will be calculated and then the differences between groups will be examined after adjusting for baseline values and surgical methods. The same methods will be used for 6 and 12 months.

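### The microbiome is left out of the plan's baseline-adjusted ANCOVA, and no named analysis uses the diet data collected beside it; this costs precision and interpretability, not validity

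*Protocol article*

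**What the plan says.** The gut microbiome is part of the secondary objective, which covers "the diversity and composition of the gut microbiome after an exercise intervention". The section on nutritional status and microbiome analysis places the FFQ and the stool sample at the same three visits (baseline, 6 and 12 months). It introduces them with the remark that "Several studies have suggested that the gut microbiota is mainly driven by nutritional status". Table 1 agrees and has a row for "Nutritional status" at those visits.

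The section on statistical analysis methods names the repeated-measures ANOVA outcomes as fasting insulin and "shoulder ROM and function, body composition, inflammatory markers, microbiome, QOL, and physical activity levels". It adds independent t-tests between arms at each time point and paired t-tests against baseline. A separate ANCOVA is planned "to test the effect of an exercise intervention on body composition, PA, and complications", with baseline values and surgical method as covariates, at 1, 6 and 12 months. Neither the microbiome nor nutritional status is among the ANCOVA outcomes, and diet is not named as a covariate anywhere.

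**The concern.** Two parts of the article do not meet. One gives a reason for measuring diet three times, namely its suggested influence on the microbiota. The other sets out which outcomes are adjusted, and for what, and gives diet no role. The analysis section also plans baseline adjustment for some outcomes and leaves the microbiome out, although its baseline value is collected.

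Two things are at stake. The first is precision for a secondary outcome in a trial that needs 80 evaluable patients. The second is interpretation: the Discussion expects microbiome changes to explain changes in other outcomes. That reading is hard to defend if diet by arm is not reported next to the microbiome result.

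**Working it through.** The plan gives no figure on this point to reproduce. The check is a comparison of the text, followed by arithmetic for scale.

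**1. Text side by side**

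| Item | Visits | Repeated-measures ANOVA | ANCOVA outcome | ANCOVA covariate |
|---|---|---|---|---|
| Microbiome | baseline, 6, 12 months | named | not named | not named |
| Nutritional status (FFQ) | baseline, 6, 12 months | not named | not named | not named |
| Body composition | baseline, 1, 6, 12 months | named | named | baseline value |

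Two tests are planned without a list of variables: t-tests of continuous variables at baseline, and t-tests of variables between arms at each time point. FFQ intake can fall under both.

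**2. Gain from the baseline microbiome value**

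Let ρ be the correlation of a microbiome index between baseline and follow-up, with equal variances. The documents do not give ρ; 0.5 is assumed, with 0.3 and 0.7 as a range. The variance of the between-arm comparison is proportional to 1 for a follow-up t-test, 2(1 − ρ) for a change score (the contrast behind the group-by-time test), and 1 − ρ² for ANCOVA. The sample-size equivalent of the gain is the ratio of variances minus 1.

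| ρ | Against follow-up t-test | Against change score |
|---|---|---|
| 0.3 | 1/0.91 − 1 = 10% | 1.40/0.91 − 1 = 54% |
| 0.5 | 1/0.75 − 1 = 33% | 1.00/0.75 − 1 = 33% |
| 0.7 | 1/0.51 − 1 = 96% | 0.60/0.51 − 1 = 18% |

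**3. Extra gain from baseline diet**

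Let R² be the share of variance that baseline diet explains, assumed 0.05, 0.10 or 0.15 and equal at both visits. Once the baseline microbiome value is in the model, only the partial share counts:

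partial R² = R²(1 − ρ) / [(1 + ρ)(1 − R²)], and gain = 1/(1 − partial R²) − 1.

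At ρ = 0.5 the factor (1 − ρ)/(1 + ρ) is 1/3.

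| R² | Partial R² at ρ = 0.5 | Gain at ρ = 0.5 | Gain at ρ = 0.3 | Gain at ρ = 0.7 |
|---|---|---|---|---|
| 0.05 | 0.05/(3 × 0.95) = 0.018 | 1.8% | 2.9% | 0.9% |
| 0.10 | 0.10/(3 × 0.90) = 0.037 | 3.8% | 6.4% | 2.0% |
| 0.15 | 0.15/(3 × 0.85) = 0.059 | 6.2% | 10.5% | 3.2% |

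With no baseline microbiome value in the model, the gain would be 1/(1 − R²) − 1 = 5.3%, 11.1% and 17.6%. That is not the relevant comparison when the baseline value is available.

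**4. Diet in the group-by-time test**

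If diet has the same effect on the index at both visits, its covariance with the change score is zero, because the two terms cancel. Adding baseline diet to that test alone then gains about nothing.

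**5. Why follow-up diet stays out of the main model**

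In a simulated model the programme has a direct effect of 0.3 and shifts follow-up diet by 0.3, and diet acts on the outcome with coefficient 0.5. The total effect is 0.3 + 0.5 × 0.3 = 0.45. The estimate is 0.448 unadjusted, 0.448 with baseline diet, and 0.298 with diet from the same visit. The last removes the part of the effect that passes through diet.

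**The case against.** The strongest objection is that this is a condensed article. The covariates for one secondary outcome, and the use of a supporting questionnaire, are often left to the full protocol or SAP. That holds for the FFQ taken alone, and it keeps the point minor. It does not dispose of the point, because the analysis section states which outcomes receive baseline adjustment and places the microbiome outside that list.

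A reader might infer several stronger things that the documents do not support:

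- **That no planned test uses diet, so a difference between arms would go unseen.** The unlisted t-tests at baseline and at each time point can include FFQ intake.
- **That the microbiome comparison is biased.** Allocation is random, so omitting baseline diet causes no bias. If the programme changes diet, that is part of its total effect.
- **That diet adjustment is worth 5 to 18% more patients.** This ignores the baseline microbiome value and, for the group-by-time test, the cancelling of a stable diet effect.
- **That only the exercise arm receives dietary influence through weekly counselling.** The weekly contact is supervised exercise, and the monthly sessions in the Abstract are exercise education and counselling. No dietary advice is described, so a diet shift in one arm is possible but not documented.
- **That the article asserts diet as the main driver.** It reports this as something that several studies have suggested.

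Adjustment also has a price: the FFQ has 109 food and 29 dish questions, so the covariates must be chosen in advance, and missing FFQs could lose patients.

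**Conclusion.** The point holds as a minor improvement. The plan leaves the microbiome out of the baseline-adjusted ANCOVA that it applies to other outcomes, and it gives the FFQ no named use. The cost is in precision and interpretability; the comparison stays valid.

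At an assumed baseline/follow-up correlation of 0.5, most of the gain (about 33% in sample-size terms) comes from the baseline microbiome value, and baseline diet adds about 2 to 6% if it explains 5 to 15% of the variance. Both inputs are assumptions. At a correlation of 0.3 and R² of 0.15, the two gains are about equal against a follow-up t-test (10% each). The case for reporting diet by arm rests on interpretation and does not depend on these figures.

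**What to change.** In the section on statistical analysis methods:

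1. Analyse microbiome diversity indices at 6 and 12 months by ANCOVA. Use the baseline microbiome value and one or two pre-specified baseline FFQ measures as covariates, beside the surgical method that the planned ANCOVA already carries.
2. Report FFQ intake by arm at 6 and 12 months, adjusted for baseline intake, next to the microbiome results.
3. State that the main comparison is not adjusted for follow-up diet. Any such analysis should be labelled as mediation or sensitivity analysis.

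The cost is a few sentences and no new data, since the FFQ and stool sample are already scheduled together. The downside is small: one or two degrees of freedom for diet, and a stated rule for missing baseline FFQs so that patients are not dropped.

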#### Statistical analysis methods

All analyses will be performed using the SPSS version 26.0 software (IBM Corp., Armonk, NY, USA). A Chi-square test for categorical variables and an independent t-test for continuous variables will be used to test group differences at baseline. Two-way repeated-measures ANOVAs will be conducted to observe the effects of the intervention on fasting insulin levels, shoulder ROM and function, body composition, inflammatory markers, microbiome, QOL, and physical activity levels. Paired t-tests will be performed to examine the difference between outcome measurements and baseline values, while independent t-tests will be employed to examine group differences in variables at each time point. The Bonferroni correction method will be used to correct for multiple tests. Analysis of covariance (ANCOVA) will be applied to test the effect of an exercise intervention on body composition, PA, and complications, since these variables will be measured after adjusting for baseline values. First, from baseline to 1 month from the baseline will be calculated and then the differences between groups will be examined after adjusting for baseline values and surgical methods. The same methods will be used for 6 and 12 months.

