#### Sample size

The calculation for sample size was based on a previous study that evaluated the effects of 16 week mixed strength and endurance exercise on insulin levels in patients with breast cancer [31]. Based on a power of 80%, two-sided statistical significance level of 5%, and medium-sized effect size, the minimum required sample size would be 80 participants. Considering the dropout rate to be 20%, 96 patients with breast cancer are needed for the current study.

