## Randomization

Eligible participants will be randomly assigned to the exercise or control group, considering age, surgery method, and neoadjuvant chemotherapy as potential confounders. Each group would be matched into pairs such that the average age, surgical method, and neoadjuvant chemotherapy percentage are approximately equal (1:1 ratio). The exercise group will be provided with a systematic exercise program from post-operative day (POD) 1 to 12 months after surgery. The control group will receive the same preoperative and post-operative medical care and treatment as the exercise group (i.e., the usual care group thereafter), except for post-operative exercise. To evaluate the effects of the exercise intervention, measurements will be conducted five times for all the participants. The registration number of the Korean Clinical Trials Registry is KCT0007853. Data will be de-identified for analysis, and only study leaders at the university hospital will have access to identifiable information for all participants.

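### The primary outcome is fasting insulin at 12 months, but the plan names no 12-month primary test and leaves insulin out of the baseline-adjusted analysis it gives other outcomes

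*Protocol article*

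**What the plan says.** The primary objective and the section on primary outcome measures both point to 12 months. Insulin is sampled at baseline, 6 and 12 months, and the 12-month visit carries the primary-outcome label. The Abstract is looser: "The main outcome of the study is fasting insulin level at baseline, 6 months, and 1 year post-intervention".

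Under Statistical analysis methods:

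- For insulin and most other outcomes: "Two-way repeated-measures ANOVAs will be conducted to observe the effects of the intervention on fasting insulin levels". Independent t-tests without covariates are added for group differences at each visit, and paired t-tests for change from baseline.
- On multiplicity, one general sentence: "The Bonferroni correction method will be used to correct for multiple tests". No family or number of tests is given.
- ANCOVA is assigned to body composition, physical activity and complications, where "the differences between groups will be examined after adjusting for baseline values and surgical methods". Body composition and physical activity also stand in the repeated-measures ANOVA list.

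Under Randomization, the arms are balanced "considering age, surgery method, and neoadjuvant chemotherapy as potential confounders". The Sample size section reads "Based on a power of 80%, two-sided statistical significance level of 5%, and medium-sized effect size", giving 80 evaluable and 96 randomised participants.

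**The concern.** The trial's main question is whether fasting insulin at 12 months differs between arms. The plan offers at least two candidate answers. One is the group-by-time term of a three-visit ANOVA, which is a 2-degree-of-freedom test of any difference in profile. The other is a 12-month t-test that ignores the participant's own baseline value. Neither is designated primary, so which p-value decides the trial is left open.

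The more efficient method is already in the plan but is not given to the primary outcome. The allocation factors are also absent from the insulin analysis; only surgical method enters a model, and only for other outcomes. At stake are power in a trial of 96 participants and protection against choosing among tests after the results are known.

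**Working it through.** **Can the ANCOVA paragraph be read as covering insulin?** No. Insulin is not among its listed outcomes. The paragraph also starts from the change to 1 month, and Table 1 schedules no serum markers at that visit.

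**Inputs from the protocol.** Two-sided 5%, 80% power, a medium effect with no number, 80 evaluable (Sample size); 1:1 allocation (Randomization), so 40 per arm; insulin at baseline, 6 and 12 months (Primary outcome measures, Table 1).

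**Assumed.** Standardised difference d = 0.5 at 12 months; equal correlation ρ between visits, 0.3 to 0.7; 6-month effect x between 0 and 0.5; no baseline difference.

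**1. The plan's own figure.** With d = 0.5, a two-sample comparison needs 2 × (1.960 + 0.842)² / 0.5² = 62.8, so 63 per arm or 126 in total (128 with the t distribution). The stated 80 does not come out this way. At 40 per arm the detectable d at 80% power is 0.63. A between-group repeated-measures ANOVA with f = 0.25 gives 78 (three visits, ρ = 0.4) or 86 (ρ = 0.5), but those settings are not stated. The basis of the 80 is a separate matter; here 40 per arm is taken as given.

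**2. Unadjusted t-test at 12 months.** Noncentrality 0.5 × √(40/2) = 2.236 on 78 df gives 60% power. At 0.05/2 it is 48%; at 0.05/3 it is 42%.

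**3. Baseline-adjusted ANCOVA at 12 months.** Residual variance is the fraction 1 − ρ² of the unadjusted variance, so the effective difference is 0.5/√(1 − ρ²): 0.524, 0.577, 0.625 and 0.700 at ρ = 0.3, 0.5, 0.6 and 0.7.

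**4. Group-by-time test.** F with 2 and 156 df, noncentrality (40/2) × SS/(1 − ρ), where SS is the sum of squared deviations of (0, x, 0.5) from their mean. SS is 0.125 at x = 0.25 (its minimum) and 0.167 at x = 0 or 0.5. At ρ = 0.6 the noncentrality is 20 × 0.125/0.4 = 6.25, or 20 × 0.167/0.4 = 8.33.

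| ρ | ANCOVA | t-test | Group-by-time (x = 0.25 to x = 0 or 0.5) |
|---|---|---|---|
| 0.3 | 64% | 60% | 37–47% |
| 0.5 | 72% | 60% | 50–62% |
| 0.6 | 79% | 60% | 59–73% |
| 0.7 | 87% | 60% | 73–85% |

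Against the t-test the gain runs from 64 − 60 = 4 to 87 − 60 = 27 points. Against the group-by-time test it runs from 87 − 85 = 2 to 64 − 37 = 27 points.

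**5. Does this depend on d = 0.5?** The ordering of ANCOVA and t-test does not. With d = 0.634 the t-test has 80% power at 40 per arm. ANCOVA at ρ = 0.5 then has 90%, and the Bonferroni t-test has 71% (two tests) or 65% (three).

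**The case against.** The best defence is that repeated-measures ANOVA and t-tests are conventional in a randomised pre-test/post-test design and hold their type I error under their assumptions. The primary objective speaks of change in insulin, which group-by-time addresses. That test can also come close to ANCOVA: 85% against 87% at ρ = 0.7. The effect size, the correlation and the 6-month effect are all assumed, and at ρ = 0.3 ANCOVA gains only about 4 points over the t-test. All of this stands. It limits the size of the point and its severity, but it does not supply a named 12-month test or a reason to leave out baseline insulin.

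A reader might infer more, and the protocol does not support it:

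- **That the ANOVA discards everyone with a missed visit.** A classical repeated-measures ANOVA would, but the protocol states neither the procedure nor a missing-data rule. That detail may sit in an analysis plan not shown.
- **That the group main effect, which averages in baseline and has low power, is the planned test.** The protocol does not say so; group-by-time is the ordinary reading.
- **That Bonferroni certainly splits the primary test's alpha.** The sentence is general and may concern only follow-up comparisons. The 48% and 42% figures apply only if it covers the primary test, over two or three tests.

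**Conclusion.** The point holds as a should-fix. The text is clear: a 12-month primary outcome, no 12-month primary contrast, no baseline adjustment for insulin, and two competing analyses for body composition and physical activity. An analysis plan would have to depart from the published wording to cure this.

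The cost in power is about 2 to 27 points, given d = 0.5, 40 per arm, equal correlations of 0.3 to 0.7 and a 6-month effect between 0 and 0.5. Its direction was the same at every correlation tried; its size cannot be fixed from the document. If Bonferroni reaches the primary test, there is a further mismatch with a sample size set at a full 5%.

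It would go too far to call the planned analysis invalid. The defect is one of efficiency and of an unspecified primary test. Nor does the protocol establish a need for a log scale.

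**What to change.** 1. Name one primary test: the exercise-minus-control difference in fasting insulin at 12 months, adjusted for baseline insulin, age, surgical method and neoadjuvant chemotherapy, at two-sided 5%.
2. Preferably estimate it from a mixed model of the 6- and 12-month values using all available data. A 12-month ANCOVA with the same covariates is simpler but not equivalent, because it omits participants without a 12-month value.
3. State that Bonferroni applies to secondary tests only.
4. Give body composition and physical activity one analysis, the baseline-adjusted one.

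The cost is revised wording and slightly different code. Baseline insulin is already scheduled, and the three other covariates are already needed for allocation. The change should be made before outcome data are examined.

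### Single-step Bonferroni is valid but needlessly conservative: Holm's step-down procedure keeps the same 5% familywise error and never rejects less (optional improvement)

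*Protocol article*

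**What the plan says.** The relevant text is in the protocol article, under Statistical analysis methods. It plans repeated-measures ANOVAs for the "effects of the intervention on fasting insulin levels, shoulder ROM and function, body composition, inflammatory markers, microbiome, QOL, and physical activity levels", so the paragraph covers the primary outcome (fasting insulin) and the secondary outcomes together. It then plans paired t-tests against baseline, and states that "independent t-tests will be employed to examine group differences in variables at each time point". The next sentence is the whole of the multiplicity plan: "The Bonferroni correction method will be used to correct for multiple tests".

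The section does not say which tests form a family or how many there are. It mentions no confidence intervals. An ANCOVA for body composition, physical activity and complications is described after the Bonferroni sentence.

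The only error rate and power in the article are under Sample size: "Based on a power of 80"%, a "two-sided statistical significance level of 5"% and a "medium-sized effect size" with no number attached. They belong to the insulin-based sample size.

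**The concern.** Single-step Bonferroni compares every p-value in a family of m tests with 0.05/m. Holm compares only the smallest p-value with that limit and relaxes the limit after each rejection. The error guarantee is the same, so a test that Holm would reject and Bonferroni would not is lost without any return in error control.

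This could matter here because the trial is small and looks at both short- and long-term effects. Table 1 schedules shoulder range of motion and strength, SPADI, quality of life, body composition and physical activity at three visits after baseline, and serum markers and microbiome at two. Bonferroni loses most where an effect persists over several tests of one family. At stake is some power per test. The validity of the conclusions is not affected.

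**Working it through.** **The plan's own figure.** The article gives no figure for the Bonferroni correction, so there is none to reproduce. Its sample size supplies the arm size: "Considering the dropout rate to be 20%, 96 patients with breast cancer are needed for the current study". With 20% lost, 96 × 0.8 = 76.8, or about 38 per arm.

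**Inputs**
- Familywise level: 0.05, two-sided (Sample size section).
- Evaluable patients: 38 per arm, as above; 1:1 allocation (Randomization section).
- Standardised difference d = 0.5 for each real effect: an assumption, a common reading of a medium effect.
- Correlation between tests 0.5: an assumption.
- Number of tests m = 2 or 3: an assumption, matching the two or three visits after baseline in Table 1.

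**Rules.** Order the p-values p(1) ≤ … ≤ p(m).
- Bonferroni: reject each p ≤ 0.05/m.
- Holm: for j = 1, 2, …, reject p(j) as long as p(j) ≤ 0.05/(m − j + 1), and stop at the first failure.

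For m = 3 the Holm limits are 0.05/3 = 0.0167, 0.05/2 = 0.025 and 0.05. Bonferroni uses 0.0167 three times.

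**Why Holm never rejects less.** Every Holm limit is at least 0.05/m. The p-values at or below 0.05/m come first in the ordering, so each passes its Holm limit.

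**Why the error is the same.** Suppose m₀ of the m hypotheses are true. When Holm reaches the first true one, at most m − m₀ others have been rejected, so the limit is at most 0.05/m₀. A false rejection therefore needs at least one of m₀ true p-values to be ≤ 0.05/m₀. That has probability at most m₀ × 0.05/m₀ = 0.05, whatever the dependence.

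**Illustration.** With p = 0.010, 0.020 and 0.040, Bonferroni rejects only the first. Holm rejects all three (0.010 ≤ 0.0167, 0.020 ≤ 0.025, 0.040 ≤ 0.05).

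**Size.** Exact t-test power for one test with 38 per arm and d = 0.5 is 57.6% at 0.05, 46.1% at 0.05/2 and 39.9% at 0.05/3. Simulation adds the Holm column:

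| Tests in family | Real effects | Power per real effect, Bonferroni | Power per real effect, Holm |
|---|---|---|---|
| 3 | 3 | about 40% | about 47% |
| 3 | 2 | about 40% | about 43% |
| 3 | 1 | about 40% | about 40% |
| 2 | 2 | about 46% | about 52% |

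Repeat runs differ by up to about one point. With no real effect and m = 3, familywise error was 4.6% for both methods. No Bonferroni rejection was lost under Holm in any run. The chance of at least one rejection was identical in every scenario, as it must be: both methods judge the smallest p-value against 0.05/m.

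**The case against.** The strongest reply is that Bonferroni is a valid, prespecified method that controls familywise error under any dependence. Nothing in the article is misstated or contradicted, and the same remark could be made about every plan that names Bonferroni. That stands, and it is why this is an optional improvement. It does not remove the point, because Holm is at least as good for every family at the same error rate. Its usual drawback, the lack of simple simultaneous intervals, costs nothing that this section plans.

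Three stronger readings are tempting, and the article does not support them.

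- *The plan gives away power on the secondary outcomes.* The correction is not tied to secondary outcomes, since the paragraph includes fasting insulin. The number of tests is not given, and no power is promised for secondary outcomes. The loss cannot be read from the document.
- *The trial needs significance at all three visits.* Under the assumptions above, the chance of showing an effect at all three would rise from 16% to 30%. No stated objective sets that target.
- *The gain is large.* At d = 0.65, with an effect at all three visits, power per visit goes from 65% to 73%. But 0.65 appears nowhere in the article, and the programme is built on phase-dependent effects with a different goal for each phase. An effect concentrated in one visit is plausible, and the gain is then about zero.

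The t-test simulation also does not represent the ANCOVA. The ordering argument does carry over to any valid p-values, so only the size of the gain is affected. Whether the planned 80 and 96 patients follow from the stated inputs is a separate question and has no bearing here.

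**Conclusion.** The point holds as an efficiency improvement. That Holm keeps the 5% familywise error and never rejects less is a mathematical result and needs no assumption about the family, the effect size or the correlation.

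The size of the gain is conditional. With 38 per arm, d = 0.5 and correlation 0.5 it ranges from about zero (one real effect) to about 7 percentage points per test (three real effects out of three). A reader might infer that the stated correction is wrong or endangers the trial's conclusions; the article does not support that. Whether a family shows any significant result at all is the same under both methods.

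**What to change.** Optional: in Statistical analysis methods, replace the Bonferroni correction by the *Holm step-down correction at the same two-sided 5% familywise level*, applied to the same sets of tests that the plan intends for Bonferroni. This change need not redefine those sets.

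The cost is small. It needs no further patients or data, only sorting the p-values within each set and comparing them with the stepped limits. It should be made before outcome data are compared by group. The downside is that Holm has no simple matching simultaneous confidence intervals. If unadjusted intervals are reported beside Holm-adjusted p-values, they should be labelled as unadjusted, because such an interval can exclude zero while the adjusted p-value is above 0.05.
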